## Abstract

**Introduction:**

Attention-deficit hyperactivity disorder (ADHD) is characterised by symptoms of inattention, hyperactivity and impulsivity. To improve outcomes, the National Institute for Health and Care Excellence ADHD guidelines recommend regular monitoring of symptoms when children commence medication. However, research suggests that routine monitoring rarely happens, and clinicians often rely on subjective information such as reports from parents and teachers to ascertain improvement. These sources can be unreliable and difficult to obtain. The addition of an objective test of attention and activity (QbTest) may improve the objectivity, reliability and speed of clinical decision-making and so reduce the time to identify the optimal medication dose. This study aims to assess the feasibility and acceptability of a QbTest medication management protocol delivered in routine healthcare services for children with ADHD.

**Method and analysis:**

This multisite feasibility randomised controlled trial (RCT) will recruit 60 young people (aged 6–17 years old), diagnosed with ADHD, and starting stimulant medication who are seen by Child and Adolescent Mental Health Services or Community Paediatric services. Participants will be randomised into one of two arms. In the experimental arm (QbTest protocol), the participant will complete a QbTest at baseline (prior to medication initiation), and two follow-up QbTests on medication (2–4 weeks and 8–10 weeks later). In the control arm, participants will receive treatment as usual, with at least two follow-up consultations. Measures of parent-, teacher- and clinician-rated symptoms and global functioning will be completed at each time point. Health economic measures will be completed. Clinicians will record treatment decision-making. Acceptability and feasibility of the protocol will be assessed alongside outcome measure completion rates. Qualitative interviews will be conducted.

**Ethics and dissemination:**

The findings will be used to inform the development of a fully powered RCT. The results will be submitted for publication in peer-reviewed journals. The study has ethical approval.

**Trial registration number:**

NCT03368573; Pre-results.

Strengths and limitations of this studyThe study uses a pragmatic intervention randomised controlled trial (RCT) design conducted in routine National Health Service settings.Adding QbTest to routine care for medication management has not yet been attempted in the UK. In line with Medical Research Council guidelines on complex interventions, we need to first establish the feasibility of the research design.The protocol was co-created with a multidisciplinary team of experts, including healthcare professionals, patient and public involvement members, expert statisticians and health economists, and academics.If the protocol is deemed feasible and acceptable, a further fully powered RCT would be necessary to determine the health and economic impact of adding QbTest to medication management for attention-deficit hyperactivity disorder.

## Introduction

Attention-deficit hyperactivity disorder (ADHD) affects 3%–5% of children and young people under 18 years old.^1^ The core symptoms include inattention, impulsivity and hyperactivity leading to significant impairments in academic and social function and increased risk of substance misuse, unemployment, criminality and mental health problems.^2 3^ Early treatment is crucial to improve symptoms and reduce the burden on the family and wider social and healthcare systems.^4^ With the increasing rates of diagnosis of ADHD, spending on ADHD medication has increased sevenfold between 1998 and 2005,^5^ and expenditure on medication treatment costs in the UK is now estimated at £78 million per year.^5 6^ This has placed increasing financial burden on health services and highlighted the need for more efficient and cost-effective services to diagnose and treat the condition. Indeed, the National Institute for Health and Care Excellence (NICE) guidelines^1^ emphasise the importance of young people with ADHD having access to the best evidence-based care in order to fulfil their potential and prevent poor outcome. However, in practice, delivery and quality of care is variable with little consistency in diagnosis or management.^7^ Improving child and adolescent mental health services is a current government priority.^8^

NICE ADHD guidelines^1^ recommend frequent monitoring of ADHD symptoms in children and young people prescribed medication to ensure first, that the best dose of medication is reached quickly for each child and second, that the effectiveness of this dose is monitored regularly, ensuring optimal outcomes are maintained with minimal side effects. The US National Institute of Mental Health Multimodal Treatment Study of ADHD (MTA)^9^ showed that frequent symptom monitoring with careful adjustment of the dose significantly improved outcomes in ADHD. In this study, the proportion of children that experienced a clinically significant reduction in symptoms was almost 60% compared with only 25% for those not subjected to this careful monitoring procedure.^9^ While treatments for ADHD are highly efficacious in carefully managed research settings,^1^ in standard community care careful monitoring is rarely possible and the outcome of treatment may be suboptimal. Audit data within the East Midlands showed that community care for ADHD falls well below the standards for titration and monitoring set out in the MTA and NICE guidelines.^7^ Aside from delays in initiating treatment caused by diagnostic uncertainty, once on medication, children may not be reviewed sufficiently frequently for clinicians to detect non-response or partial response, or to establish the optimal dose for each child. Research has demonstrated that families are often unhappy with the length of time to attain reach an optimal dose of medication (up to 18 months), with very few participants reporting titration was achieved in the 6-week time frame advocated by NICE.^10^ These issues mean that children may not experience the full benefits of medication and this has significant negative effects on their academic, social and psychological development. A further consequence of suboptimal treatment response in routine care is poor medication adherence. In the UK, 50% of patients have stopped ADHD medication after 18 months and 80% after 3 years.^11^

Current methods to judge the effectiveness of medication rely on the clinician integrating various forms of subjective information, information such as clinical rating scales completed by parents and teachers, with their own observations. However, the information provided by these sources can be contradictory, partially completed or not returned in a timely manner leading to delays in treatment decisions. Adding more objective, computerised tests to clinical care for ADHD is one approach which has received increasing clinical and research recognition.^12^ The continuous performance test (CPT) is a computerised neuropsychological test that measures the individual’s capacity to sustain attention (vigilance) and inhibit inappropriate responses (impulsivity). Several studies have noted improvement in CPT scores in children with ADHD on stimulant medication^13–15^ indicating the potential utility of these tests to aid medication management in clinical practice. However, there is a need for further research on CPTs examining the clinical utility and cost-effectiveness using randomised controlled trials (RCTs).^16^ Furthermore, a limitation of the CPT is that it does not measure the patients’ activity levels, which is a core symptom domain of ADHD. A recent systematic review^16^ indicated that a combination of a CPT with objective direct measure of bodily activity during the test may be particularly useful as a clinical tool. One test that combines the CPT with a measure of activity is the ‘QbTest’ (Qbtech, www.qbtech.com), a commercially available measure of ADHD symptoms approved by the Food and Drug Administration (FDA) (Reference: K133382). The QbTest takes approximately 20 min to complete, during which time the child/young person is seated in front of a computer and is instructed to press a hand-held responder button each time a predesignated infrequent target stimulus appears on-screen, and to withhold the response to all other stimuli. These features of QbTest measure sustained and selective attention (target detection over 600 stimulus presentations), and impulsivity (withholding the response to a non-target). Simultaneously, an infrared camera tracks the movement of a marker attached to a headband worn during the test, to measure activity. All young people aged 6–17 years can sit the QbTest providing they do not have moderate/severe learning difficulty. The test provides a summary score relevant to each symptom domain (inattention, hyperactivity, impulsivity) with reference to a large age-stratified and gender-stratified normative database.^17^ The QbTest should not be used to reach a decision about diagnosis or medication without additional clinical information but aids decision-making by providing another source of information, reducing reliance on questionnaires.

Recent research has investigated the use of the QbTest to aid in the clinical assessment of ADHD. QbTest can help differentiate ADHD from other conditions^18–20^ and audit data suggests that QbTest can reduce the number of appointments needed to confirm a diagnosis of ADHD and result in cost savings to health services.^21^ A recent RCT with health economic analysis further investigated whether the QbTest can reduce the number of appointments needed to make a diagnostic decision on ADHD.^22^ Initial qualitative findings from this trial indicate that the QbTest is acceptable to children and families and feasible to implement in routine clinical settings.^23^ Furthermore, the qualitative interviews revealed that some clinicians currently use QbTest to: improve confidence in diagnosis before initiating medication; reassure families, young people and schools of medication efficacy to improve adherence and review medication effects at follow-up to aid decisions around dose adjustment.^23^ These findings highlight the potential clinical utility of the QbTest in medication management. In support of this, other research has shown that QbTest is sensitive to the effects of stimulant medication^24^ and, in a placebo-controlled trial of atomoxetine that performance improvements correlate with blinded observer ratings of ADHD symptoms.^25^ It has also shown some utility in identifying partial or non-responders after a single dose of methylphenidate.^26^ Another study in adults with ADHD showed that the QbTest was more sensitive to medication effects than a standardised rating scale.^27^

Although promising, few of these previous studies were conducted in the UK. Moreover, although some clinics within the UK, Europe and the USA are using QbTest to aid medication management, there is no standard approach and most clinics still rely on traditional approaches of using rating scales and clinical judgement. There is a need to formally evaluate the role of the QbTest to aid medication management in ADHD and assess whether the test should be routinely incorporated in healthcare services. In line with the Medical Research Council guidance on evaluating complex interventions (interventions (www.mrc.ac.uk/complexinterventionsguidance), the aim of this ‘QbTest Utility for Optimising Treatment in ADHD’ (QUOTA) study is to assess the feasibility and acceptability of a novel QbTest medication management protocol in a parallel group, single-blind, feasibility RCT with embedded qualitative evaluation. To ascertain the clinical utility of the protocol in standard practice, treatment as usual (TAU) was the chosen comparator. The findings from this study will be used to inform the decision to conduct a fully powered, definitive RCT investigating whether QbTest can help reduce the time to reach an optimal, effective medication dose.

## Methods and analysis

QUOTA trial commenced on 1 April 2017 and consists of two stages: stage 1 consisted of a series of three expert workshops which were conducted with the aim of designing QUOTA research protocol. Stage 2 consists of the feasibility RCT.

### Stage 2: feasibility RCT

#### Trial design

The study is a parallel group, single-blind multicentre feasibility RCT, which explores feasibility and acceptability of a QbTest medication management protocol, using quantitative, qualitative and health economic evaluations. The trial is registered with ClinicalTrials.gov (www.clinicaltrials.gov; NCT03368573) and is at the pre-results stage. The study flow is outlined in figure 1. The trial consists of two arms.

**Figure 1 F1:**
[figure not shown]
Participant flow diagram. ADHD, attention-deficit hyperactivity disorder; CAMHS, Child and Adolescent Mental Health Services; CGI, Clinical Global Impressions Scale; CHU9D, Child Health Utility; SDQ, Strengths and Difficulties Questionnaire; SNAP-IV, Swanson, Nolan and Pelham IV.

##### Experimental arm (QbTest group)

In this arm, participants will receive standard TAU plus three QbTests. The participant will complete a QbTest at baseline, prior to medication initiation (if a QbTest has not already been completed <12 weeks prior to medication initiation as part of their diagnosis), and again at follow-up 1 (2–4 weeks later) and follow-up 2 (8–10 weeks later). The clinician will use the QbTest scores to inform their clinical decision-making regarding medication decisions (ie, to inform titration, drug choice or treatment switch/termination).

##### Control arm (TAU)

In this arm, participants will receive standard TAU. However, to provide some control over the possible increased clinical contact in the experimental arm, clinicians are requested to make at least two contacts with the participant during the 12-week follow-up period. These contacts may take place over telephone.

The patients usual care team will be responsible for conducting the QbTest in clinic appointments. The QbTest will be only be conducted by trained QbTest clinicians. Although TAU differs across sites/clinicians’/cases, it typically involves clinical interviews with the parents/carer/young person to ascertain improvement in symptoms, and sometimes collection of standardised outcome measures. The TAU care practices will be recorded on a specifically created clinician-completed pro forma (see the Measures section). There are no prohibited concomitant interventions. Given this study is assessing the feasibility of the protocol no measures will be taken to improve protocol adherence.

### Recruitment and eligibility

Recruitment is scheduled to start 1 December 2017. Patients with a confirmed ADHD diagnosis and commencing stimulant medication for ADHD will be invited to participate in the research based on the following criteria:

#### Inclusion criteria

age 6–17 years old (at the time of consent)male or femalereferred to CAMHS or Community Paediatric servicesdiagnosed with ADHDclinician and family (parent/carer and young person/child) agreement to commence stimulant medication for ADHD symptomscapable of providing written informed consent (over 16 years old)parental consent (under 16 years old).

#### Exclusion criteria

unable to provide informed consentsevere learning disability (to be assessed by clinical judgement)non-fluent Englishnot commencing stimulant medication (either not started on medication at all or started on a non-stimulant medication).

Eligibility will be determined by the treating clinician who has read and approved the protocol. Written information about the trial will be provided to families by their treating clinical team at the point where a decision to start stimulant medication has been agreed. There are four types of participant information sheets: one for parents/caregivers, one for young people aged 16 years and older, one for young people aged 12–15 years old and one for children aged 6–11 years old. The information sheets were developed with our PPI group.

Clinicians will be encouraged to ask patients if they have any questions/queries before signing consent and will have sufficient knowledge of the research protocol to answer anticipated questions. Families may consent into the study at the appointment they first receive the information sheet, once they have had time to discuss the study and ask any questions with the clinician. The PPI group felt this would not put undue stress on families and was necessary to avoid any delays in medication initiation for those wishing to participate. Clinic invitations will be updated on a password-protected database, recording numbers invited, numbers declined and reasons for decline. Each site will be informed of their monthly recruitment target required in order to meet the target sample size.


SNAP-IV,^35^ SDQ,^36^ CGI,^37^ CHU9D^38^ and side effects scale^33^ have established reliability, validity and history of use in clinical and research settings. As this is a feasibility study, there are no plans to promote retention and follow-up measure completion, but completion rates will be recorded to inform the future RCT.

Additionally, a subsample of 10–15 participants (parents/carers and/or young people) in the experimental arm will be interviewed about their experiences of the trial, including their opinion on randomisation; within this subsample, we will include participants who did not complete the trial, if possible, acknowledging that the views and experiences of non-completers may also provide useful insight into acceptability. A subsample of 10 in the control arm will be interviewed about their experiences of ADHD medication. The subsample will be chosen at random from each participating site, using a random number generator. All clinicians participating in the feasibility RCT will be interviewed, and asked to comment on any local factors that influenced delivery of the protocol at their site, providing early insight into factors that might influence delivery of the multisite RCT and future implementation of the protocol into the NHS. All interviews will take place after their duration in the RCT has been completed to avoid any impact on outcome measures. Interviews will be digitally recorded, transcribed and analysed. The results of these interviews will be used to inform any refinement of the protocol to improve its acceptability before embarking on the definitive RCT.

Table 1 displays the study measures, the informant and the time point of completion. All measures will have a 1-month window for completion, with the exception of the clinic pro forma which must be just after the clinic appointment and the QbTest which will be completed within the specified time frame. For participants who withdraw from the trial, the outcome measures already collected will be included in analysis, and no further outcome measures will be collected.

**Table 1 T1:** Table of study measures

Measure (and informant)	Baseline	Follow-up 1 (2–4 weeks)	Follow-up 2 (8–10 weeks)
SNAP-IV (P&T)	x	x	x
SDQ (P&T)	x		x
CGI (C)	x		x
CHU9D (P&YP)	x	x	x
Medication adherence (P&YP)		x	x
Side effects (P&YP)		x	x
QbTest (YP)*	x	x	x
RUSH (P)			x
RUSE (T)			x
Pro forma (C)†	x	x	x
Subsample for interview (P, YP, C)			x

*Experimental arm only.

†Pro forma completed at every appointment.

C, clinician; CGI, Clinical Global Impression Scale; CHU9D, Child Health Utility; P, parent/carer; RUSE, Resource Use—Services in Education; RUSH, Resource Use—Services for Health; SDQ, Strengths and Difficulties Questionnaire; SNAP-IV, Swanson, Nolan and Pelham 4th edition; T, teacher completed; YP, young person.

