### Sample size and justification

The required sample is 60 participants, 30 per study arm. Participants will be families (parents/carers and children/young people) whose child/young person is about to commence stimulant medication for ADHD. These sample sizes are large enough to test the feasibility of the research procedures and to establish a mean and SD on each outcome measure (Hertzog; 2008). The study has an 8-month recruitment period, requiring 7.5 participants to be recruited into the study each month. Based on findings from the AQUA-Trial (which included the three sites used in this trial) this target is achievable. Recruitment rates and the final target will be used to inform the decision to proceed to a definitive RCT.

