### Data analysis plan

As a feasibility study, data analysis will be mainly descriptive, as recommended by Lancaster^39^ and Lancaster *et al*.^40^ All measures will be summarised by group across follow-up time with mean (SD) for normally distributed data, median (IQR) for skewed variable and frequency (percentage) for categorical measures. Together with site-level intraclass correlation coefficient, treatment effects and 95% CI will be derived using multilevel modelling. Recruitment rate and retention rate will also be calculated from the data. This information will be used to inform the future definitive RCT design. All statistical analysis will be conducted using STATA V.15. No interim analysis is planned.

To inform the acceptability and feasibility of the study design the following indices will be recorded and analysed: (1) *acceptability of randomisation*—record of the number of patients who do not participate stating randomisation as the reason for non-participation, drop-out rates of randomisation, errors in randomisation per site; (2) *acceptability of study design*—record of the number of eligible participants at each site and the percentage that consent to take part in the study, number of withdrawals at each follow-up time point; (3) *acceptability of outcome measures*—record of completion rates for outcome measures, percentage of data collected online, via telephone or postal completion; (4) *acceptability/feasibility of the protocol*—record of non-adherence of healthcare professionals to the protocol. These reasons will be further explored in the qualitative interviews and (5) *feasibility of a future definitive RCT*—record an estimate of the hours per week spent conducting the RCT and estimate the number of researchers required and the time commitment for healthcare professionals in a future RCT.

The qualitative interviews will shed light on contextual and other factors that might affect implementation of QbTest (both as part of the trial, and within the broader processes of care) and will be used to refine the RCT design (and QbTest implementation more broadly) if appropriate. The qualitative interviews will be transcribed verbatim and analysed thematically following the guidelines of Braun and Clarke.^41^ The quantitative and qualitative findings will be used to determine the feasibility and acceptability of the medication protocol and research study design, and inform the decision to proceed to a fully powered RCT.

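### As described, the family interviews would give no control-arm view on randomisation, allocation to usual care or questionnaire burden, although they help decide whether the trial design is acceptable

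*Protocol article*

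**What the plan says.** All the interview statements are in the Measures section of the protocol article.

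- **Experimental arm:** the plan says "a subsample of 10–15 participants (parents/carers and/or young people) in the experimental arm will be interviewed". The topic is broad, since families "in the experimental arm will be interviewed about their experiences of the trial, including their opinion on randomisation".
- **Control arm:** "A subsample of 10 in the control arm will be interviewed about their experiences of ADHD medication". Neither the trial nor randomisation is named.
- **Non-completers:** the experimental-arm sentence continues "within this subsample, we will include participants who did not complete the trial, if possible", because their views may inform acceptability. Nothing equivalent is said for the control arm.
- **Selection:** "The subsample will be chosen at random from each participating site, using a random number generator".
- **Clinicians:** all are interviewed. The stated topic is local factors affecting delivery.

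The Data analysis plan lists acceptability of randomisation, of the study design and of the outcome measures as feasibility indices. For randomisation the first index is a "record of the number of patients who do not participate stating randomisation as the reason for non-participation". Drop-out, randomisation errors by site, consent percentage, withdrawals at each follow-up and questionnaire completion are also recorded. The same section says that quantitative and qualitative findings together will settle whether the protocol and the research design are feasible and acceptable, and will inform the decision to proceed. Measures adds that the post-intervention interviews will help select the primary outcome of the definitive trial.

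**The concern.** Whether families accept randomisation and the burden of the study is one of the questions this trial exists to answer. Half of the families are allocated to usual care. Under Randomisation and blinding they complete the same research measures as the other arm apart from QbTest, and the clinician opens the envelope at the point of consent. They know from experience what it is like to be randomised and not receive the new test. Experimental-arm families cannot report that.

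If the control interviews follow the stated topic, the investigators will have family accounts of the trial from one arm only when they decide on the definitive RCT. A count can show that control families withdrew or returned fewer forms, but not why. A control family that stays in the study while unhappy with its allocation appears in no count at all.

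The second, smaller issue is that the plan wants non-completers in the experimental-arm subsample but describes a selection rule that does nothing to secure them.

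**Working it through.** **1. The plan's own figures.** "The required sample is 60 participants, 30 per study arm", and 30 + 30 = 60. The recruitment rate also reproduces: 60 / 8 months = 7.5 per month. No stated figure is in dispute.

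**2. Who is asked about randomisation, as written.**

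| | Interviewed | Stated topic includes trial and randomisation |
|---|---|---|
| Experimental | 10–15 | 10–15 |
| Control | 10 | 0 |
| All families | 20–25 | 10–15 |

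The share asked is 10/20 = 50% to 15/25 = 60%, all from one arm. With the same questions in both arms, 20–25 families would be asked, 10 of them controls.

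**3. What the other sources cover.**

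- *Refusals and reasons for decline* concern families who never entered. They say nothing about living with an allocation.
- *Withdrawals, drop-out and completion rates* are not limited to one arm, and the Data analysis plan summarises all measures by group. Excess control-arm loss would show. These indices give numbers and do not state that reasons for withdrawal will be recorded.
- *Clinician interviews* have local delivery as their stated topic.

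None of these gives a control family's own account.

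**4. Non-completers under random selection.** Let d of the 30 experimental-arm families be non-completers and n be drawn at random. The chance that none is drawn is C(30 − d, n) / C(30, n). The article gives no drop-out rate, so d is an assumption.

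- d = 3, n = 10: (20 × 19 × 18) / (30 × 29 × 28) = 6840 / 24360 = 0.281
- d = 3, n = 15: (15 × 14 × 13) / (30 × 29 × 28) = 2730 / 24360 = 0.112

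| Assumed non-completers of 30 | Draw of 10 | Draw of 15 |
|---|---|---|
| 1 | 67% | 50% |
| 2 | 44% | 24% |
| 3 | 28% | 11% |
| 5 | 11% | 2% |
| 6 | 6.5% | 0.8% |

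Drawing by site changes little. Assume 10 experimental-arm families at each of the three sites and one non-completer per site. A draw of 4 + 3 + 3 then misses all three with probability 0.6 × 0.7 × 0.7 = 29%, and a draw of 5 + 5 + 5 with probability 0.5³ = 12.5%.

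These figures describe a purely random draw. They do not allow for the stated intention to include non-completers.

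**The case against.** **The interviews are not the only evidence on acceptability.** This stands, and it limits the point. A reader might infer that acceptability would be judged from the experimental arm alone, or that control-arm drop-out would go undetected. The documents do not support that. The Data analysis plan counts refusals, drop-out, withdrawals and completion without limiting them to one arm, and Recruitment and eligibility provides for a record of reasons for decline. What is missing is the control families' explanation.

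**No bias has been shown.** This also stands. It is tempting to say that control families are the most likely to object, that disappointment with usual care drives drop-out, or that acceptability will look better than it is. Nothing in the article supports any of these. The families most opposed to randomisation may never consent, and they would appear among the refusals. Only the possibility of a one-sided account can be claimed.

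**The topic guide may be broader than one phrase.** The article does not say that medication is the only control-arm topic, and the full protocol is available on request. That is fair, and a broader guide would resolve the point. But the article does more than stay silent: two nearby sentences give the arms different scopes, and only one names the trial and randomisation.

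**The plan already intends to include non-completers.** It does, so the fault is the lack of a stated mechanism and not a lack of intent. The two sentences could be read together as random selection with non-completers added where they agree. Any rule depends on their willingness to be interviewed. This part is therefore secondary.

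**Conclusion.** The point holds in a limited form. Followed as written, the family interviews yield no control-arm view on randomisation, on being allocated to usual care or on questionnaire burden: 0 of 10 control interviews against 10–15 of 10–15 in the experimental arm. Those interviews feed the judgement on the research design, so the qualitative part of that judgement may be one-sided. The quantitative indices are unaffected, and the validity of the trial is not in question. The conclusion assumes that the control-arm topic guide matches the article's description.

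The non-completer issue is an unreconciled pair of statements. Its size depends on an unknown drop-out rate. Over the assumed range of 1 to 6 non-completers of 30, a purely random draw would miss all of them with probability 67% down to 6.5% for 10 interviews, and 50% down to 0.8% for 15.

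**What to change.** 1. **Control interviews.** Add the trial-experience questions used in the experimental arm to the 10 control interviews already planned: opinion on randomisation, being allocated to usual care, and the burden of the questionnaires. Keep the medication questions. If the topic guide already covers this, say so in the protocol.
2. **Selection.** State how the aim of including non-completers works with the random draw. For example, first invite non-completers in each arm who are willing to be interviewed, then fill the remaining places at random by site. If at least one willing non-completer exists, the chance of missing all of them is then zero by design.

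No additional participants or interviews are needed. The cost is slightly longer control interviews, a changed selection rule and possibly a minor ethics amendment to the topic guide. Both changes need to be in place before the interviews begin.
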